**Methods:**

This parallel-group, 1:1, outcome assessor-blinded, individual adaptive RCT investigates whether completing the BBC intervention plus hand hygiene twice-daily at home increases OME resolution after 4-to-6 weeks in children with OME, compared to hand hygiene alone. Families (n = 250) perform their individually randomized program (BBC plus hand hygiene, or hand hygiene only) at home. The primary outcome is the difference in OME resolution rates between trial arms, assessed using tympanometry (type B to A or C_1_ transition) and otoscopy. Secondary outcomes include natural OME resolution, discharges from tertiary care, family satisfaction, hearing thresholds, QoL, bacterial load in the nasopharynx and on hands, cost comparison within the RCT versus standard care, and adverse events. All outcomes are measured by blinded researchers. An intention-to-treat analysis will be performed on all randomized participants. Guided by an Aboriginal Community Advisory Group, the RCT ensures culturally appropriate research whilst addressing community priorities in managing childhood ear disease.

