### Eligibility criteria

4.3

Children and their families need to meet all the following inclusion criteria to participate:1.Aged between two and seven years old.2.Clinical referral indicates hearing or ear related concerns.3.Able to attend all study visits regardless of residential location within Western Australia.4.Persistent OME, defined as two type B tympanometry results documented by a health professional at least three months apart within a 12-month period in the same ear (unilateral or bilateral), with or without hearing loss. These results can be sourced from the child's medical records or collected during screening visits for the RCT. Inclusion of children with persistent OME aligns with the 2020 Otitis Media Guidelines, which recommend intervention when OME persist for three months or longer [4]. To determine eligibility based on persistent OME, children and their families are offered up to three screening visits.

Children and their families are excluded if any of the following exclusion criteria are met:1.Scheduled to undergo surgical intervention for OME within the next four weeks.2.Current or previous diagnosis of cleft lip and/or palate, Down syndrome, major chromosomal anomalies, craniofacial anomalies, chronic suppurative otitis media, or congenital ear anomalies.3.Concurrent participation in another interventional ear study.4.Unable to engage with study procedures due to any physical, medical, developmental, behavioral or cognitive condition(s).5.Parent(s)/carer(s) decline to cease using non-study ear clearing interventions during the intervention or control period (any ear treatments that are not clinically prescribed).6.Clinical inclusion criteria for persistent OME are not met (inclusion criteria no. 4 above).7.Share a household with a current or previously participating child.

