### Outcomes

4.5

The primary outcome measure is the proportion of children that experience OME resolution in the intervention arm compared to the control arm, assessed through tympanometry. Tympanometry is a diagnostic test of middle ear function using parameters such as peak pressure, compliance, and ear canal volume, which tracks the transition from type B result (indicative of OME) at enrolment (week 0) to a type A result (normal) or type C_1_ result (Eustachian tube dysfunction, suggesting resolving OME) at post-randomization (week 4-to-6) (Table 2) [30,40]. For this study, a type A tympanogram is defined as a peak pressure of > −100 daPa, a type B tympanogram has an indeterminable peak pressure, a type C_1_ tympanogram as a peak pressure of between −100 and −199 daPa, and a type C_2_ tympanogram as a peak pressure of −200 to −400 daPa [41]. Type C_1_ tympanograms will be considered indicative of resolved OME in addition to type A tympanograms, as the literature suggests type C_1_ may reflect a transient or resolving stage of middle ear effusion, rather than a persistent form of OME requiring intervention [16,41]. Resolution can be unilateral or bilateral, however the primary outcome will only be considered in any ears that produced type B tympanograms at enrolment. Type C_2_ tympanogram findings will be considered indicative of ongoing middle ear dysfunction. The efficacy of the BBC intervention will be considered clinically meaningful if it results in a number needed to treat to benefit (NNTB) of 10 or less for the resolution of OME.

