Secondary outcome measures include: (1) rate of natural OME resolution, evidenced by a transition of type B tympanograms to type A or C tympanograms; (2) proportion of otolaryngology/audiology care discharges, evaluated using multidisciplinary team (MDT) and clinician review outcomes from enrolment to final follow-up (weeks 24-to-32); (3) family satisfaction with care provision through the RCT, assessed using a survey at final follow-up, (4) four-frequency hearing thresholds measured by audiometry at enrolment, post-randomization, and final follow-up; (5) QoL, assessed through the Otitis Media-6 (OM-6), Parent-evaluated Listening and Understanding Measure (PLUM), and Hearing and Talking Scale (HATS) questionnaires at enrolment, post-randomization, and final follow-up; (6) bacterial loads, quantified as the densities of all bacteria species of interest at enrolment and post-randomization, analyzed using high-throughput qPCR on samples collected from the nasopharynx and palms of hands; (7) cost-of-service comparison for OME diagnosis and management through the study compared to standard care via economic analysis; and (8) the proportion of adverse events, monitored through safety data collection from enrolment to final follow-up. Refer to Table 2 for a comprehensive schedule of data collection methods and collection timepoints for participants in both trial arms.

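### No entry criterion requires a type B ear at week 0, although the primary outcome exists only in such ears; natural resolution also uses a wider definition than the primary outcome

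*Protocol article*

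**What the plan says.** **Primary outcome (4.5).** Resolution is a change from type B at enrolment (week 0) to type A or C1 at weeks 4 to 6, and "the primary outcome will only be considered in any ears that produced type B tympanograms at enrolment". On the two C types, C1 "tympanograms will be considered indicative of resolved OME in addition to type A tympanograms", while C2 "tympanogram findings will be considered indicative of ongoing middle ear dysfunction".

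**Eligibility (4.3).** Inclusion 4 defines persistent OME as "two type B tympanometry results documented by a health professional at least three months apart within a 12-month period in the same ear". The results may come from "medical records or collected during screening visits for the RCT". Exclusion 6 only restates inclusion 4. Exclusion 1 reads "Scheduled to undergo surgical intervention for OME within the next four weeks".

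**Natural resolution (4.5, secondary outcome 1).** This is "evidenced by a transition of type B tympanograms to type A or C tympanograms". Section 4.10 estimates it from pre-enrolment screening data and from control-arm participants.

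**Analysis set.** The abstract promises intention-to-treat on all randomised participants. Section 4.11 limits the primary analysis to eligible participants who reach weeks 4 to 6. The model in 4.10 needs a 0 or 1 for each participant analysed.

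**Abstract.** The primary outcome is "assessed using tympanometry (type B to A or C_1_ transition) and otoscopy".

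**The concern.** Eligibility and the primary outcome are both stated in this article, and they do not fit together. Inclusion 4 looks back over earlier tests, and its 12-month span is not tied to the enrolment date. The primary outcome looks only at ears that are type B on the day of enrolment. A child whose effusion cleared after the second recorded type B result meets every written criterion, can be randomised, and then has no ear that can resolve or fail to resolve.

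The restriction in 4.11 does not remove this child, who is eligible as the criteria are written and does reach weeks 4 to 6. Someone must later decide, possibly after data have accrued, whether the child is dropped or scored as not resolved. The choice affects the trial's power, and dropping the child departs from the abstract's intention-to-treat statement.

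The second mismatch concerns what counts as resolved. A control child who moves from B to C2 is resolved under natural resolution and not resolved under the primary outcome.

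**Working it through.** **1. Can the gap occur?** Take a child with two type B results in one ear, four months apart, both in the medical record, whose ear is type A at week 0.
- Inclusion 4: met.
- Exclusion 6: not triggered.
- Primary outcome: no ear was type B at enrolment, so it is undefined.
- Abstract: the child was randomised, so is included.
- Section 4.11: the child is eligible and reaches weeks 4 to 6, so is included.

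The text allows the case and does not say how to score it.

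**2. The plan's own power figure.** Section 4.6 gives control rates of 14% to 20%, a 13-point increase, 5% type I error, a maximum of 250 participants and power of about 80%. With n = 125 per arm and a one-sided two-proportion test,

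z = [Δ√n − 1.645·√(2·p̄·(1−p̄))] / √(p0(1−p0) + p1(1−p1)).

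At 17% versus 30%, p̄ = 0.235. The numerator is 0.13 × 11.180 − 1.645 × 0.5996 = 1.4534 − 0.9864 = 0.4671. The denominator is √(0.1411 + 0.2100) = 0.5925. So z = 0.788 and power is 78.5%. At control rates of 14% and 20% the results are 81.9% and 75.5%. The stated 80% is reproduced on a one-sided reading for control rates of 14% to 17%.

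**3. Baseline under the stated Bayesian rule.** Inputs from 4.10 and 4.11:
- looks at 100, 150, 200 and 250 completers
- superiority if P(β1 > log 1.1) > 0.975, futility if it is < 0.05
- α ~ N(logit 0.17, 0.3²) and β1 ~ N(0, 1)

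Pathway terms are omitted. By simulation, power at 17% versus 30% is about 70%. This is the baseline for step 4. Its distance from 80% is a separate matter and comes from a simplified model.

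**4. Sensitivity to f, the share with no type B ear at week 0.** The article gives no value, so f is an assumption.
- *Left out:* the rates stay at 17% and 30%, and each look has (1 − f) of its completers.
- *Counted unresolved:* both rates are multiplied by (1 − f). At f = 10%, 0.17 × 0.90 = 15.3% and 0.30 × 0.90 = 27.0%, so the difference is 11.7 points instead of 13.

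| f | Left out | Counted unresolved |
|---|---|---|
| 0% | about 70% | about 70% |
| 5% | about 68% | about 63% |
| 10% | about 66% | about 55% |
| 20% | about 60% | about 41% |

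Repeat runs vary by a few points. The simple test of step 2 at f = 10% gives 74.6% (left out) and 73.5% (unresolved), against 78.5%.

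**5. The two resolution definitions.**

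| Change from B to | Primary outcome | Natural resolution |
|---|---|---|
| A | resolved | resolved |
| C1 | resolved | resolved |
| C2 | not resolved | resolved |

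On the same children, the natural-resolution rate can only equal or exceed the rate by the primary definition. The article gives no C2 frequency, so the excess cannot be sized.

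**6. Windows.** Exclusion 1 covers four weeks and the outcome is read up to week 6. Section 4.2 recruits children already referred for surgery. Surgery after week 4 but before a week 6 visit is compatible with the text.

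**The case against.** The strongest reply is that current OME is plainly intended. The research question concerns children with OME, and randomisation is stratified by OME class with only unilateral and bilateral as levels. Table 2 places eligibility, tympanometry and randomisation together at week 0. The flow figure and the full protocol are not available here. This is good evidence of intent, but none of it is an entry criterion, and the criteria that are printed do not require it.

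A second reply is that the power loss may be small or nil. If looks counted only children with an evaluable ear, power would be kept at the price of recruiting more: 250 / 0.90 = 278 completers at f = 10%. Leaving such children out is also the handling closest to section 4.5, and it is the milder case. Both points stand, and they limit the size of the problem.

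A third is that natural resolution is a descriptive secondary outcome and may have its own definition. It may, but the article gives no reason for calling C2 unresolved in one place and resolved in another, and the control arm feeds both.

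Three stronger readings are tempting and are not supported:
- A reader might infer that type I error is inflated because cleared ears are counted as resolved. Section 4.5 confines the outcome to ears that were type B at enrolment, so that analysis is ruled out.
- A reader might infer that surgery will decide some primary outcomes. The introduction cites surgical waits of six to twelve months, a week 4 visit could precede surgery, and handling may be set out elsewhere.
- A reader might infer that the abstract is wrong about otoscopy. Section 4.9 lists video-otoscopy among the outcome tools and Table 2 makes it mandatory at weeks 4 to 6, so the article does not settle which text is intended.

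**Conclusion.** The concern holds in two parts. First, the written criteria allow a child to be randomised with no ear on which the primary outcome is defined, and the article does not say how such a child is scored. This is something the text permits; nothing shows that it has happened or how often it would. If the share were 10%, power would fall by about 4 points (left out) or about 15 points (counted unresolved) from a baseline of about 70%. Over 5% to 20% the loss runs from about 2 to 10 points and from about 7 to 29 points respectively. These sizes rest on an assumed share, rates of 17% and 30%, and a model without pathway terms.

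Second, natural resolution and the primary outcome classify a B-to-C2 change in opposite ways, and control children contribute to both. The direction is certain and the size is unknown.

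The surgery window and the otoscopy wording are lesser inconsistencies.

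**What to change.** 1. Add to inclusion 4 that the qualifying ear must be type B on the week 0 study tympanogram, taken before randomisation. Table 2 already makes this test mandatory. The cost is a short amendment and a few screened children who become ineligible.
2. In secondary outcome 1, replace type A or C with type A or C1, so that control children are classified in one way. This is a wording change.
3. Reconcile the four-week surgery exclusion with the week 4 to 6 outcome window, given the surgical recruitment pathway. No particular rule is proposed here.
4. Reconcile the abstract and section 4.5 on whether otoscopy is part of the primary outcome. The sponsor should say which is intended.

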### Sample size

4.6

Power analysis was used to understand the trial operating characteristics, assuming a range for the proportion of OME resolution in the control arm to be between 14 % and 20 % [16]. Assuming a moderate 13 % absolute increase in OME resolution at post-randomization in the intervention arm compared to the control arm and type one error controlled at 5 %, the power is estimated to be approximately 80 % for a maximum sample size of 250 participants. Accounting for 10 % loss-to-follow-up, the RCT intends to recruit up to 275 participants to achieve sufficient power to declare superiority of the BBC intervention plus hand hygiene.

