### Interim analysis and decision criteria

4.11

The RCT will involve regular Bayesian updates to assess pre-planned decision criteria efficiently, ensuring timely answers to research questions [59]. The pre-planned adaptations include stopping recruitment for superiority or futility based on the primary analysis. The first interim analysis will occur after 100 eligible participants have completed the four-to-six-week post-randomization follow-up (referred to as ‘completers’), and subsequent updates for every 50 additional completers for the remainder of the RCT. Only data for eligible participants reaching weeks 4-to-6 will be used in the primary analysis.

Decision criteria for superiority and futility were identified using trial simulation to control for power and type one error. The BBC intervention plus hand hygiene will be declared superior at a pre-specified analysis, and recruitment into the trial may stop if the decision ruler for superiority is met:$$P\left(\beta_{1}>\log\left(1.1\right)\right)>0.975$$

Alternatively, at a pre-specified analysis, the trial may stop recruitment for futility if the decision rule for futility is met:$$P\left(\beta_{1}>\log\left(1.1\right)\right)<0.05$$

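### The printed superiority rule gives about 63 to 74% power for the 13-point effect at 250 completers, not the stated approximately 80%, so sections 4.6 and 4.11 do not fit together

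*Protocol article*

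**What the plan says.** Section 4.6 (Sample size) sets the planning assumptions. The control rate comes from "assuming a range for the proportion of OME resolution in the control arm to be between 14 % and 20" per cent. The effect is given as "Assuming a moderate 13 % absolute increase in OME resolution at post-randomization", and the error rate as "type one error controlled at 5" per cent. The result is that "the power is estimated to be approximately" 80% with at most 250 participants. For 10% loss, "the RCT intends to recruit up to 275 participants to achieve sufficient power", so 250 is read here as completers. The abstract gives 250 for the families taking part: "Families (n = 250) perform their individually randomized program".

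Section 4.10 gives a Bernoulli-logit model with intercept α ~ N(logit 0.17, 0.3²) and treatment and pathway log odds ratios each N(0, 1).

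Section 4.11 puts the first look at 100 completers and later looks at every further 50. Superiority is declared if P(β1 > log 1.1) > 0.975, and recruitment may stop for futility if that probability is below 0.05. Of these rules it says: "Decision criteria for superiority and futility were identified using trial simulation to control for power and type one error". Sections 4.6 and 4.11 should therefore describe one and the same simulated design.

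**The concern.** The printed rule is demanding. It asks for 97.5% posterior certainty that the odds ratio exceeds 1.1, not merely 1, and the N(0, 1) prior pulls β1 towards zero. Even an ordinary two-sided 5% test without a margin has only 65 to 72% power at this size, so 80% under a rule with a margin is surprising.

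Two things are at stake. Readers will judge a result that does not meet the superiority rule against the stated power, and the chance of missing a true 13-point gain would be higher than the 20% they are told. Also, if the simulations used a different rule, the one printed in section 4.11 is not the one whose properties were studied, and it is the one that will be applied at each look.

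**Working it through.** **Inputs.** From section 4.6: control rate 14 to 20% (midpoint 17% added), difference 13 points, 250 completers. From section 4.1: 1:1 allocation, hence 125 per arm. From section 4.10: the model and priors. From section 4.11: looks at 100, 150, 200 and 250 completers, cut-offs 0.975 and 0.05, margin log 1.1. Assumed: equal arms at each look, one binary outcome per child, no true pathway effects.

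**Step 1: can 80% be reproduced with a simple test?** For a fixed-sample z-test with n = 125 per arm and mean rate p̄,

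power = Φ( [δ − z·√(2p̄(1−p̄)/n)] / √([p0(1−p0) + p1(1−p1)]/n) ).

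At 17% v 30%: p̄ = 0.235, null SE = √(2 × 0.235 × 0.765/125) = 0.0536, alternative SE = √((0.1411 + 0.2100)/125) = 0.0530.
- Two-sided 5%: (0.13 − 1.96 × 0.0536)/0.0530 = 0.47, power 68%.
- One-sided 5%: (0.13 − 1.645 × 0.0536)/0.0530 = 0.79, power 78.5%.

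At 14/17/20% the results are 72.4/68.1/64.5% (two-sided) and 81.9/78.5/75.5% (one-sided). The one-sided test comes near 80%, but it is not the section 4.11 rule.

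**Step 2: hand check of the printed rule, final look only, 17% v 30%.** The normal approximation on the log-odds scale gives:
- Control information 125 × 0.17 × 0.83 = 17.64; intercept prior adds 1/0.3² = 11.11; total 28.75, variance 0.0348.
- Intervention-arm variance 1/(125 × 0.30 × 0.70) = 0.0381.
- Variance for β1 before its own prior: 0.0348 + 0.0381 = 0.0729. The N(0, 1) prior multiplies the estimate by 1/(1 + 0.0729) = 0.932.
- True log odds ratio 0.738; expected posterior mean 0.932 × 0.738 = 0.688; posterior SD √(0.0729 × 0.932) = 0.261.
- Sampling SD of the posterior mean: 0.932 × √(0.0381 + (17.64/28.75)²/17.64) = 0.227.
- Power ≈ Φ((0.688 − 0.0953 − 1.96 × 0.261)/0.227) = Φ(0.36) ≈ 64%.

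The grid calculation for a single look at 250 gives 62.4%, so the two agree closely.

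**Step 3: the printed design with all four looks.** The posterior of β1 was computed on a grid for every pair of arm counts, with 200,000 simulated trials per scenario.

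| Rule | Power at control 14 / 17 / 20% | Type I error, no effect |
|---|---|---|
| Printed: margin log 1.1, cut-off 0.975 | 62.5 / 68.9 / 74.4% | 0.3 / 0.9 / 2.3% |
| Margin log 1.1, cut-off 0.95 | 75.8 / 80.4 / 84.2% | 0.8 / 2.4 / 5.2% |
| Zero margin, cut-off 0.975 | 76.2 / 81.4 / 85.3% | 0.8 / 2.4 / 5.3% |

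Binding and non-binding futility give the same power within simulation error. Adding three pathway terms with no true pathway effects gives 63 to 70% with equal shares and 63 to 73% with shares of 60/20/20.

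**Step 4: the loss allowance.** 275 × 0.9 = 247.5 expected completers, while 250/0.9 = 277.8, or 278. The gap of 2.5 completers has a negligible effect on power.

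**The case against.** Four points can be made for the plan.

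*Other readings of the size.* Recruitment may reach 275, and looks continue every 50 completers. If nobody were lost and a last analysis were made near 275 completers, power would be 68/73/78%. That narrows the gap at a 20% control rate but still does not reach 80%, and it contradicts the plan's own 10% loss.

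*Pathway effects.* If some pathways resolve materially more often, simulated power rises to about 80%. The overall rates and difference then leave those stated in section 4.6. Pathways with lower rates take power down to about 50 to 61%.

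*The simulations are not shown.* This stands in part. A report or analysis plan may describe scenarios that the article does not. But the article prints every input of its own claim, and the claim does not follow from them.

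*Type I error.* An error of 0.3 to 2.3% does satisfy a 5% limit, and a superiority declaration under the printed rule is not inflated. If the error is instead evaluated at an odds ratio of 1.1, it is 0.7/2.2/4.9%, which also fits that limit. So the type I statement alone does not show that the rule is misprinted.

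That last point bears on a stronger reading. A reader might infer from the 0.95 row that the cut-off is the misprint. The zero-margin row fits equally well, and it remains possible that the rule is right and the power figure wrong. The documents do not settle which.

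**Conclusion.** The stated power is wrong for the design as printed. Under sections 4.10 and 4.11, power for the 13-point effect is about 63%, 69% and 74% at control rates of 14%, 17% and 20%. That is a shortfall of 6 to 18 points, and of 11 at the intercept prior's own centre of 17%. The chance of missing the effect is about 37%, 31% and 26%, against the 20% implied. "Approximately" does not cover a gap of that size. The result assumes 250 completers, equal arms and no true pathway effects.

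Two further inferences are not supported. The finding does not show that a superiority declaration would be unsafe, because the printed rule is conservative under no effect. Nor does it show that the trial must recruit more: about 320 completers would give 80% at a 17% control rate under the printed rule, but that only shows the scale of the gap. The loss allowance of 275 rather than 278 is a minor slip, and the abstract's 250 agrees with the stated maximum.

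**What to change.** Check the existing simulation code before an interim look applies the rule, and establish which margin and cut-off it used. Then make one of two corrections:

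- If the code used the printed rule, restate power in section 4.6 as about 62 to 75% over control rates of 14 to 20% (about 69% at 17%), with the type I error that the rule achieves.
- If the code used another margin or cut-off, print that rule in section 4.11 with its power and type I error. This is a correction only if that rule was the one simulated at planning. A looser rule should not be adopted now merely to recover 80%.

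In either case, say whether the 5% refers to an odds ratio of 1 or of 1.1, and that 250 means completers. If the text is being edited anyway, 278 is the arithmetically consistent recruitment figure for 10% loss.

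The cost is a check of existing code, a few edited lines and, under the first correction, a less favourable stated power. No extra patients are needed.
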